#### Focus groups

Utilizing a data driven approach informed by the collected quantitative data on feasibility and acceptability metrics, we will conduct focus groups to further explore feasibility constructs. A purposive sampling procedure will be employed whereby a sub selection of eligible participants who completed LightBEAM and indicated interest in completing a focus group will be asked to participate after they complete their six-month follow-up surveys. Proposed purposive criteria may include focus groups sampled based on gender, immigrant status, program adherence, and ethnicity. By utilizing such purposive criteria, focus groups will also allow authors to explore how the program served specific populations. In total, 2–3 groups of 5–7 participants per purposive criterion will be conducted. Focus groups will take place over Zoom and be approximately 1.5 h long. Research has demonstrated that focus groups conducted via Zoom evidence high participant satisfaction, strong data quality and improved access for participation [2]. Both audio and video will be recorded, however, only audio recordings will be transcribed and analyzed. Audio recordings will be uploaded to Trint for transcription purposes. Confidentiality will be ensured by instructing participants to refrain from mentioning any personal identifiable details during the focus group (e.g., refrain from saying their or others’ name). If any identifying details are said, these will be redacted from the transcripts. As part of signing the consent form, participants will also be asked to respect fellow participants' privacy and refrain from sharing participant information learned within the interview/focus group.

A manifest content analysis approach guided by established frameworks (e.g., Theoretical Framework of Acceptability; Sekhon et al. [31]) will be used to enhance data quality. Several strategies will be employed to code qualitative data. Established coding rules will determine inclusion criteria and guide interpretation of ambiguous data to ensure consistency across coding team. Phrases and sentences that reflect a distinct idea related to feasibility, acceptability, or user experience will be defined as single unit of analysis. Once coding rules are established, transcripts will be double coded to generate initial impressions, and a series of collaborative team meetings will be used to refine candidate codes. The coding scheme will then be applied systematically across transcripts with a lead qualitative investigator reviewing coding for thematic mapping, patterning and comprehensiveness. Recommendations outlined by Begley and Tobin [36] will be utilized to further enhance trustworthiness of qualitative data including credibility, dependability, confirmability, and transferability. Several strategies will be utilized to employee these recommendations. First, during analysis, the coding team will be instructed to engaging in team-based coding and memoing to support credibility. Dependability and confirmability of data will be supported through the use of an audit trial and analytic insights. Assumptions and positionality will be addressed in team meetings to support reflexivity practices in addition to researcher journaling. Finally, transferability will be addressed by providing contextual details on participant demographics and sampling procedures. An example list of focus group questions will appear in Appendix A.

#### Compensation

Participants will be eligible to earn up to $75 CAD for participation. The compensation will be delivered in the following denominations; (a) $20 for post-intervention completion (b) $20 for completing six-month follow-up questionnaires (c) $35 for participating in optional post-intervention focus groups. Compensation will be delivered in the form an e-gift "Everything Card" which is a type of e-gift card that provides recipients with flexibility to use the funds across a wide range of retailers, both online and in-store.

### Criteria for discontinuing or modifying allocated interventions {15b}

Participants will be asked to discontinue treatment if they break the terms of use associated with the LightBEAM app which includes disclosing personal information on the group forum, engaging in inappropriate forum posts, and not respecting the privacy of other participants either on the forum or during the online orientation session. If a participant is asked to discontinue treatment, or if a participant asks to withdraw, we will email the participant and ask if we can use their partial data. If yes, data will be stored in accordance with REB study guidelines. If a participant does not consent, all partial data with the exception of the initial consent form will be destroyed.

### Strategies to improve adherence and intervention protocols {15c, 25b}

A variety of strategies will be used to increase intervention adherence including email, text and telephone reminders, all of which have improved adherence in previous BEAM trials [13, 21, 33]. Furthermore, this RCT will employ an intent to treat analysis, and as such all participants will be reminded and encouraged to complete questionnaires regardless of their level of participation in the program. Additionally, the app itself was designed with user friendly features, engaging graphics and colours and user-tested to help facilitate adherence and engagement.

#### Tracking concomitant care during trials {15d}

Participants will be allowed to receive concomitant care for mental health problems.

Use of additional interventions will be assessed through a service utilization questionnaire and subsequently controlled for in analyses to account for potential confounding effects.

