### Trial design {12}

Using a two-arm clinical design, participants will be randomized in a 1:1 allocation to be placed in either the 12-week LightBEAM program or the waitlist control. After the 12-week LightBEAM program has been completed by the intervention condition, participants in the waitlist control group will have one month to complete the “re-baselining questionnaires and online orientation prior to gaining access to the LightBEAM intervention. Participants in the intervention condition will complete post-questionnaires at the same time that the waitlist control completes re-baselining questionnaires. Longitudinal self-report questionnaires will be administered digitally at three timepoints: pre-intervention, post-intervention, and at six months follow-up.

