##### Pre-intervention, post-intervention and follow-up questionnaires

All eligible participants (i.e., main participants and co-parents) will be asked to complete additional questionnaires that assess other factors known to influence parental mental health such as sleep and self-compassion (i.e. Patient Reported Outcomes Measurement Information Symptom [PROMIS] Sleep Scale [40], The Self-Compassion Short Form Questionnaire [4, 28]). Aspects of the parent–child relationship, child development and family dynamic will also be assessed using a variety of questionnaires (i.e., The Parenting Scale, Irvine et al. [12], Child Behavioral Checklist [3]). Additionally the authors generated an emergency service utilization questionnaire (see Roos et al. [29]) and an adapted version of the National Survey for Children’s Mental Health [8] to assess various sociodemographic, service utilization and health factors related to child and family development. All questionnaires will be completed via REDCap. See Table 1 for a full list of study measures and subsequent timepoints.

**Table 1 Tab1:** Schedule for questionnaire administration: main participant

LightBEAM Proposed Metrics					
Questionnaire	Eligibility	Pre-Intervention	Re-Baselining	Post-Intervention	Follow-Up
Pre-Screener	X				
Patient Health Questionnaire	X	X	X	X	X
Sociodemographic		X			
Generalized Anxiety Disorders	X	X	X	X	X
Self-Compassion		X	X	X	X
PROMIS Anger	X	X	X	X	X
PROMIS Sleep		X	X	X	X
Parenting Stress Index	X	X	X	X	X
Social Support Effectiveness		X	X	X	X
CBCL		X	X	X	X
Parenting Scale		X	X	X	X
App Usage				X	
Service Utilization		X	X	X	X
Modified NMH		X	X	X	X

*PROMIS* Patient Reported Outcome Measurement Information Systems, *CBCL* Child Behavioral Check List, *NMH* National Survey for Children’s Mental Health, *App Usage* Author Generated App usage questionnaire

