11	Boundary setting to make space for everything else	Memory making with your kiddo
12	Staying well and moving forward	Recipe for wellness

#### Aim 2

All eligible participants must present with at least one elevated symptom of concern across parental anxiety (GAD-7), depression (PHQ-9), anger (PROMIS) and/or parenting stress (PSI). Based on which metric(s) participants screen in as being elevated, an individualized composite primary score will be created whereby we examine whether there is a statistically significant change in elevated symptoms of concern across assessment time points. To examine the efficacy of the LightBEAM program in improving parental outcomes, a multi-level model with random intercepts will be utilized to assess the effect of treatment over time based on conditions. An intent to treat approach will be followed such that all randomized participants are included in analysis, regardless of completion.

Specifically, we will examine pre-to-post-to follow up program changes in primary and secondary outcomes. Such analysis will allow us to examine the efficacy of the LightBEAM program compared to other community resources. Program engagement metrics (e.g., number of videos watched, see Table 4) will also be included as moderators to probe whether participant changes are due to program engagement. This dosage analysis will be an exploratory analysis.

**Table 4 Tab4:** Aim 1 feasibility and acceptability metrics

	Indicator	Benchmark	Rational
Recruitment Rate	Number of parents recruited per month	Approx. 50 parents	We want at least 50 parents in the forum to ensure maximum engagement
Retention Rate	% of parents with follow up data	> 70% of parents with follow up data	Average retention rate amongst previous MOOI’s is 70%
Forum Use	# of posts and comments made on the forum	> 50% of users engage at least once in the forum (i.e., through posting, responding or interacting with a message)	This is an exploratory outcome. Based on previous work that showed 57% engagement in the BEAM forum
Videos watched	% of videos watched at least 50% of the way through	Participation in > 50% of the LightBEAM Content	Utilizing same benchmark (e.g., 50%) used in previous BEAM pilot studies [13]
Symptom tracking	# of weekly surveys completed	Participation in > 50% of symptom tracking exercises	Based on benchmark used in previous BEAM pilot studies

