### Definition of analysis population related to protocol non-adherence and methods to handle missing data {27c}

The LightBEAM program will employ an intent-to-treat analysis using maximum likelihood estimation, whereby all participants, regardless of study completion and adherence, will be included in analysis based on their initial randomization. To account for treatment adherence, de-identified analyses will be conducted using only data from participants who completed the LightBEAM intervention.

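### The plan to control for concomitant service use as a confounder is not limited to use before randomisation, so it can move the arm effect away from the intention-to-treat effect

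*Protocol article*

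**What the plan says.** The section on tracking concomitant care (item 15d) has two sentences. The first is permissive: "Participants will be allowed to receive concomitant care for mental health problems". The second sets an analysis rule: "Use of additional interventions will be assessed through a service utilization questionnaire and subsequently controlled for in analyses to account for potential confounding effects". The heading and subject concern care taken while the trial runs. The rule names no measurement occasion and no model.

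Service use is collected more than once. Table 1 (main participants) and Table 2 (co-parents) both mark the service utilization questionnaire at pre-intervention, re-baselining, post-intervention and follow-up. Re-baselining applies to the waitlist arm only.

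The comparison is randomised: "participants will be randomized in a 1:1 allocation to be placed in either the 12-week LightBEAM program or the waitlist control". The efficacy analysis under Aim 2 is described thus: "a multi-level model with random intercepts will be utilized to assess the effect of treatment over time based on conditions". No covariate is listed there. The same paragraph adds: "An intent to treat approach will be followed such that all randomized participants are included in analysis, regardless of completion". The section on the analysis population (item 27c) repeats that "all participants, regardless of study completion and adherence, will be included in analysis based on their initial randomization". The blinding section says that participants and analysts know the allocation.

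**The concern.** The stated reason for the adjustment is confounding. A confounder of the arm comparison has to be associated with allocation other than as a result of it, and randomisation removes that association except for chance imbalance at baseline. Outside care taken up after allocation is different in kind. If arm alters help-seeking and the care works, service use lies on the path from arm to outcome (a mediator). If unmeasured distress drives both help-seeking and outcome, service use is also a common effect of arm and distress (a collider), and conditioning on it links the two.

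Both routes are plausible here. Waitlist parents know they are waiting, they entered with elevated symptoms, and other care is allowed. The background section itself presents LightBEAM as interim help for families waiting for individualised care. At stake is what the efficacy coefficient means: after such an adjustment it need not estimate the effect of offering LightBEAM, which is what an intention-to-treat analysis is for.

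**Working it through.** **No figure to reproduce.** The article gives no service-use rates, no effect of outside care, and no effect size or SD (the sample size of 200–500 rests on feasibility). What follows shows the mechanism under assumed inputs.

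**Identity.** Let Y be the outcome (higher is worse), S service use after randomisation (0/1), and p0 and p1 the proportions using services on waitlist and LightBEAM. In a least-squares fit of Y on arm and S,

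adjusted arm effect = total effect − k × (p1 − p0),

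where k is the pooled within-arm slope of Y on S. The total effect is the intention-to-treat difference. The shift is therefore −k × (p1 − p0). It is zero if use is equal by arm, and its sign depends on two quantities, not one. The slope k is negative when effective care dominates and positive when the greater distress of care-seekers dominates.

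**Set 1.** Assumed: direct effect −0.30; residual SD 1; effect of care b = 0 or −0.30; unmeasured distress with coefficient 0.5 on Y and latent correlation g = 0 or 0.5 with service use. Then total = −0.30 + b(p1 − p0), and

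k = b + 0.5 × [gφ(z0) + gφ(z1)] / [p0(1 − p0) + p1(1 − p1)],

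with φ the normal density at the threshold that gives each proportion. For p0 = 0.50, p1 = 0.30, b = 0, g = 0.5: k = 0.5 × (0.1995 + 0.1739) / (0.25 + 0.21) = 0.406. The shift is −0.406 × (−0.20) = +0.081. Simulation with 2,000,000 participants agreed (−0.300 against −0.219).

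| Use, waitlist / LightBEAM | b | g | Total | Adjusted | Ratio |
|---|---|---|---|---|---|
| 30% / 30% | any | any | −0.30 | −0.30 | 1.00 |
| 50% / 30% | −0.30 | 0 | −0.24 | −0.30 | 1.25 |
| 50% / 30% | 0 | 0.5 | −0.30 | −0.22 | 0.73 |
| 50% / 30% | −0.30 | 0.5 | −0.24 | −0.22 | 0.91 |
| 30% / 50% | −0.30 | 0 | −0.36 | −0.30 | 0.83 |
| 30% / 50% | 0 | 0.5 | −0.30 | −0.38 | 1.27 |
| 30% / 50% | −0.30 | 0.5 | −0.36 | −0.38 | 1.06 |

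Shifts run from about −0.08 to +0.08.

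**Set 2.** Assumed: Y = −0.30T + b_u U + b_s S + e, with e of SD 1; logit P(S = 1) = −0.2 + aT + cU, where T is arm and U unmeasured distress.

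| a | c | b_u | b_s | Use, waitlist / LightBEAM | Total | Adjusted | Ratio |
|---|---|---|---|---|---|---|---|
| 0 | 0.8 | 0.5 | −0.2 | 46% / 46% | −0.30 | −0.30 | 1.00 |
| −0.7 | 0.8 | 0.5 | −0.2 | 46% / 31% | −0.27 | −0.25 | 0.92 |
| −1.2 | 1.5 | 0.7 | −0.4 | 46% / 27% | −0.22 | −0.15 | 0.69 |
| −0.7 | 0.3 | 0.5 | −0.4 | 45% / 29% | −0.24 | −0.28 | 1.17 |
| +1.0 | 0.8 | 0.5 | −0.2 | 46% / 67% | −0.34 | −0.38 | 1.09 |
| +1.0 | 0.3 | 0.5 | −0.4 | 45% / 69% | −0.39 | −0.33 | 0.85 |

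Effects in Set 2 are in units of the residual SD; the outcome SD itself is about 1.1 to 1.2. Both sets compare arms at a single time point and do not reproduce the planned multi-level model.

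**The case against.** The strongest reply is that the sentence can be read harmlessly. It names no occasion and no model, a pre-intervention value exists, and Aim 2 lists no covariates. Adjusting for baseline use only, or adjusting in a secondary model only, would fit the words, and covariate detail commonly sits in an analysis plan that is not shown. This stands in part: adjustment for post-randomisation use is the natural reading of a rule about care during the trial, not an explicit statement. But the sentence is an affirmative rule with a wrong reason. An analysis plan that followed it on its natural reading would carry the error.

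Four stronger readings are tempting, and the documents do not support them.

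- A reader might infer that the adjustment certainly biases the result. It does so only if arm changes service use, and the article gives no evidence either way.
- A reader might infer that it removes part of the benefit, or that the direction follows from whether LightBEAM lowers or raises help-seeking. The tables show shifts of both signs for either change.
- A reader might infer that the harm could not be undone. The model without the adjustment can be fitted to the same data.
- A reader might see a contradiction with the intention-to-treat population. Those passages say who is analysed and in which arm; choosing a covariate does not breach them. The conflict is with the effect that such an analysis is meant to estimate.

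**Conclusion.** The point holds in a limited form. The article commits to controlling for concomitant service use as a confounder and does not confine this to use before randomisation. Later use is not a confounder of the arm comparison, and adjusting for it can bias the intention-to-treat effect if arm changes help-seeking.

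Neither size nor direction can be derived from the article. The ratios of adjusted to total effect (about 0.7 to 1.2 in Set 2, 0.73 to 1.27 in Set 1) rest wholly on assumed rates and effects. The lowest ratio in Set 2 needs a strong link between distress and both care-seeking and outcome. They show that a material shift is possible, not that this trial will have one. The rule is worth correcting before analysis, because analysts are unblinded and the present wording leaves open which service-use value enters the model.

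**What to change.** Amend the second sentence of the concomitant care section to say three things.

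1. The intention-to-treat efficacy model adjusts at most for service use at pre-intervention. Tables 1 and 2 already schedule this for main participants and co-parents. The article does not state outright that this questionnaire is completed before allocation, so the amended text should confirm it.
2. Service use at later occasions is reported by arm, descriptively.
3. Any analysis that adjusts for service use after randomisation is labelled exploratory, for example alongside the mediation models in the exploratory analyses section (item 27d), and is not presented as the intention-to-treat effect.

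The confounding rationale should be dropped for use after randomisation. The cost is a short text amendment; no new data or participants are needed.

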#### Sample size {19}

In total, we plan to recruit a sample of 200–500 Canadians caregivers to participate in the LightBEAM program based on recruitment success over the funding availability period [33]. Sample size was informed by feasibility based on previous BEAM trials (see Simpson et al., [33]).

## Methods: assignment of intervention {21a-b, 22, 24a-c}

### Allocation

Using the built-in randomization functionality within REDCap, participants will be randomly allocated to either LightBEAM or the waitlist control condition.

### Blinding

Study coordinators, participants, data analysts, and the principal investigator will not be blind to the condition of the participants. All randomization will be completed by the LightBEAM study coordinator using the automated REDCap randomization function. A randomization table will be created and uploaded into REDCap by a data analyst at the Canadian Centre for Health Care Innovation.

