### Statistical methods {27a, b}

Statistical analysis will occur on both IBM Statistical Package for the Social Sciences (SPSS) and Mplus 8.4. Prior to data analysis, data files will be reviewed to ensure participant questionnaire data are in the expected range and scored correctly. Missing data will be address using an intent-to-treat analysis and maximum likelihood estimation.

#### Aim 1

The feasibility of the LightBEAM program will be evaluated through examining a variety of program specific metrics including participant app usage, program attrition, and self-report implementation metrics. See Table 3 for a full list of pre-specified success criteria. Descriptive statistics (e.g., frequencies, means) will be used to examine participant program implementation metrics. Additionally, a series of qualitative questions will evaluate feasibility and acceptability in the focus groups, building off and extending the understanding of the numerical data. A manifest content analysis will be utilized to quantify and analyze qualitative focus group data. Guided by the feasibility and acceptability framework (see Sekhon et al. [31]), this approach will involve determining unit of analysis and coding rules that are applied to focus group transcripts. Next, a coding team will apply the relevant codes and share initial impressions [6]. Candidate codes will be considered and redefined in a iterative processes. Next, the coding framework will be trialed and finally first pass coding will be reviewed for comprehensiveness, patterning, and mapping.

**Table 3 Tab3:** Overview of LightBEAM weekly content

Week	Mental Health Topic	Parenting Topic
1	Values (Defining Values and Finding Motivation)	Family Values (finding and following your values)
2	Emotions + Function	Loving your whole child
3	Mindful Emotion Awareness	Helping your child name & understand their emotional experiences
4	Understanding your emotions	Emotions in the Moment (Tantrums + Coping Thoughts)
5	Emotional ARC and doing the unexpected	Meeting your child in their emotions ARC
6	Managing Emotions Reactions	Co-regulating DT + TIPP Skills
7	Anticipating Emotions and challenging moments	Pre-teaching and successful routines
8	Cognitive flexibility	Flexibility through transitions
9	Interpersonal effectiveness and clarifying priorities	Clarifying family boundaries and RESET
10	Navigating Conflict	Conflict management and STOP skills

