### Interim analysis {28b}

After the first 100 participants have completed the LightBEAM program, an interim data analysis will occur. Specifically, graduate students, principal investigators and senior research assistants will conduct preliminary analysis to assess how LightBEAM has succeeded in addressing the three proposed aims. This initial analysis will help the team identify if the translation of BEAM to LightBEAM is effective at supporting parental mental health and parenting. This will allow the team to re-evaluate the study design and implementation if results suggest we are not adequately achieving such effectiveness. De-identified analyses will be shared with larger co-investigators to assess efficacy of LightBEAM.

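### Data analysts are left unblinded, although masking them is cheap and is the only masking this self-report, waitlist-controlled trial can have; the analysis should be locked before any arm-split outcome is seen, including at the interim.

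*Protocol article*

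**What the plan says.** The Blinding section of the protocol article is explicit: "Study coordinators, participants, data analysts, and the principal investigator will not be blind to the condition of the participants". It adds that the coordinator randomises in REDCap from a table prepared by a data analyst at a separate centre.

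Outcomes come from the participants themselves. Under Trial design: "Longitudinal self-report questionnaires will be administered digitally at three timepoints: pre-intervention, post-intervention, and at six months follow-up".

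The Statistical methods section says that before analysis "data files will be reviewed to ensure participant questionnaire data are in the expected range and scored correctly". Under Aim 2, "an individualized composite primary score will be created whereby we examine whether there is a statistically significant change in elevated symptoms of concern", based on whichever of four instruments was elevated at screening, and "a multi-level model with random intercepts will be utilized to assess the effect of treatment over time based on conditions". The section on concomitant care says that use of other services will be "subsequently controlled for in analyses to account for potential confounding effects".

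The Interim analysis section says that after the first 100 participants have completed the programme, "graduate students, principal investigators and senior research assistants will conduct preliminary analysis" on all three aims. It continues: "This will allow the team to re-evaluate the study design and implementation if results suggest we are not adequately achieving such effectiveness".

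**The concern.** Against a waitlist, neither participants nor coordinators can be masked, and with digital self-report there is no outcome assessor. The analyst is the only person between the participant's answer and the effect estimate who could work without knowing the arm. The plan gives this up without stating a reason.

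This matters because, as the article stands, the analysis has open choices. The primary score combines one to four instruments whose screening thresholds (5, 5, 14 and 110) show very different scales, and no rule for scaling or combining them is given. The form of the adjustment for concomitant care is also open, as is the contrast across pre, post and follow-up that decides efficacy. If these are settled with outcomes by arm in view, they can drift, even without intent, towards the version that favours LightBEAM. The interim analysis adds to this, because results by arm are seen by the people who may then change the design.

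**Working it through.** **1. Is masking restored anywhere else?** No. The sections on non-adherence and interim analysis mention de-identified analyses, but that hides who the participant is, not the allocated arm. The article describes no coded arm label, blind data review or masked statistician, and the Monitoring section says there will be no formal data monitoring committee.

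**2. Which steps can knowledge of the arm reach?**

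| Step | Fixed before randomisation? | Exposed? |
|---|---|---|
| Which metrics enter a participant's score | Yes, at the eligibility screener | No |
| Range and scoring checks | No | Yes |
| Scaling and combining the metrics | Not in this document | Yes |
| Covariates, including concomitant care | Not in this document | Yes |
| Contrast that decides efficacy | Not in this document | Yes |
| Design changes after the interim | No | Yes |

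**3. When is the interim?** Under Trial status, the first 100 participants finish their 12 weeks in July 2025, and recruitment ends by December 2025. On the plan's own dates, the look can therefore fall while recruitment is still open. It covers all three aims, and the second is the comparison with the waitlist.

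**4. Can analysts be masked?** Largely, for the randomised comparison. Trial design has the intervention arm's post-intervention questionnaires and the waitlist arm's re-baselining questionnaires completed at the same time, so both can carry one 12-week label. App-usage fields reveal the arm and would have to be removed. Later visits differ by arm, and the engagement and completer analyses rest on app use, so those cannot realistically be masked.

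**5. How large could the effect be?** The plan states no alpha, power or effect size, so there is nothing to reproduce. This is an illustration on assumed inputs: two defensible scorings, null test statistics Z1 and Z2 that are bivariate normal with correlation r = 0.8, and a two-sided 5% test (critical value 1.96). The analyst reports whichever scoring favours LightBEAM more.

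- Joint tail: J = P(Z1 > 1.96 and Z2 > 1.96) = 0.0110. By symmetry, the joint lower tail is the same.
- Favourable error: P(max(Z1, Z2) > 1.96) = 0.025 + 0.025 − J = 0.0390.
- Unfavourable error: P(max(Z1, Z2) < −1.96) = J = 0.0110.
- Two-sided total: 0.0390 + 0.0110 = 0.0500.

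The favourable tail rises from 2.5% to 3.9%, the unfavourable tail falls from 2.5% to 1.1%, and the total is unchanged. With r = 0.7 the favourable tail is 4.2%; with r = 0.9 it is 3.5%.

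**The case against.** **Open declaration.** Unmasked analysis is stated plainly, contradicts nothing else, and is a design choice in a trial whose sample size was set by feasibility. That stands, and it limits the point to a recommended improvement.

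**A separate analysis plan.** A statistical analysis plan not shown here may fix the composite, covariates and contrast. If it does so before any arm-level look, the consequence shrinks. The stated lack of masking remains.

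**Coding the arms A/B is not enough.** This is correct. An analyst with an arm-split file can still see differences between groups while choices are open. Selection is prevented by fixing the choices before any arm-split outcome is seen; coded arms come after that.

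**A larger error rate.** A reader might infer that unmasked analysts push the 5% error to about 8%. With r = 0.8, picking the smaller of the two p-values in either direction does give 2 × (0.05 − J) = 7.8%. But that needs no knowledge of which arm is which, so an analyst working with A/B labels could do the same. It measures the cost of an unfixed composite, not of unmasked analysts. A simulated 9.5% to 11.5% for the smallest p-value among four composites (assumed inputs) has the same limitation.

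**No cost, or wider benefit.** A reader might also infer that masking is free, that one team is known to clean, score and model the data, or that masking would cure reporting bias. The documents support none of these. The re-baselining label and app data have to be handled, the data review is described without saying who does it, and participants know their arm when they answer.

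**Conclusion.** The point holds as a low-cost improvement that should be made; it is not a fatal flaw. The article states that analysts are unblinded, nothing elsewhere offsets this, and the analysis is the only stage at which this trial could be masked. The exposure is confined to cleaning, scaling and combining the metrics, covariates, the contrast, and what follows the interim; it does not extend to which metrics form a participant's score. The size cannot be derived from the documents. Under the assumption of two scorings correlated 0.8, choosing in LightBEAM's favour moves the favourable-tail error from 2.5% to about 3.9% with the two-sided total at 5.0%. This shows what open choices could do and is not evidence that they would be misused. The conclusion assumes that no unseen analysis plan already locks these choices before the interim.

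**What to change.** Amend the Blinding section, with a cross-reference from Interim analysis, as follows.

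1. Finalise and lock data cleaning, composite derivation and primary model code on pooled data without the arm variable. Relabel the waitlist re-baselining questionnaires as the common 12-week visit and remove app-usage fields.
2. Complete this lock before any arm-split outcome is seen, including at the interim analysis.
3. Run the randomised post-intervention comparison on arms coded A/B. Someone outside the study team holds the key until that result is final, for example the centre that prepares the randomisation table.
4. Run the follow-up, engagement and completer analyses unmasked with the locked code, and say so, because visit structure or app data reveal the arm.

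The cost is a recoded export, a key-custody duty that the outside centre would have to accept, and a short delay to the unmasked analyses. No extra participants, visits or measures are needed. The amended text should also acknowledge that participants' unblinded self-report remains a source of bias that this change does not address.
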